## Abstract

**Background:**

Rheumatoid arthritis (RA) is the most common type of autoimmune arthritis affecting 0.5–1% of the adult population worldwide. While the primary line of treatment of RA includes pharmacological therapies, people living with the condition often seek non-pharmacological therapies such as diet and exercise in an attempt to attenuate their symptoms. Established, evidence-based dietary guidelines for RA are currently lacking. The MEDRA study aims to explore the effectiveness of implementing, via telehealth, a Mediterranean type diet (MedDiet) compared to a standard healthy diet as per the Healthy Eating Guidelines (HEG) in Ireland in terms of differences in physical function and quality of life in adults with RA living in Ireland.

**Methods:**

The MEDRA study is a parallel, randomised controlled trial delivered through telehealth methods. Forty-four eligible participants who have RA will be randomly allocated to either a MedDiet or HEG group for a 12 weeks intervention period. Primary outcome measures include changes in physical function and quality of life, both of which will be measured using validated questionnaires at baseline, six and twelve weeks. Both intervention arms will attend a total five teleconsultations with a Registered Dietitian (RD). The MedDiet intervention arm focuses on recommendations from the traditional Mediterranean diet and HEG intervention arm will use the dietary recommendations as currently advised in Ireland.

**Discussion:**

This study will provide evidence as to whether dietary treatment of RA can improve physical function and quality of life in a small cohort of participants with RA. The results of the study will be disseminated at national scientific conferences and published in peer-reviewed journals.

**Ethics:**

This protocol has been approved by the Education and Health Sciences Research Ethics Committee at the University of Limerick (2020_09_05_EHS) and by the Health Service Executive Mid-Western Regional Hospital Research Ethics Committee (REC Ref 103/19).

**Trial registration:**

ClinicalTrials.gov NCT04262505. Trial registration date: April 2, 2020.

## Background

1

Rheumatoid arthritis (RA) is a chronic autoimmune inflammatory disease that primarily affects the joints of the hands and feet, causing malformation and damage to these joints [1]. RA is the most prevalent form of inflammatory polyarthritis affecting 0.5–1% of the global adult population [2]. The condition is three times more common in women than in men with a typical age of onset between 40 and 50 years [3]. RA can affect nearly all organs in the body leading to co-morbid conditions [4]. The prevalence of comorbid conditions reported in different studies varies between 40 and 66% [[5], [6], [7]]. The most commonly reported comorbidities are cardiovascular diseases, gastrointestinal disorders, infections, osteoporosis and depression [8]. The physical function and quality of life of people with RA are severely impacted due to the nature of the condition and the increased risk of morbidities associated with it [9]. Treatment for RA involves lifelong pharmacological adherence to delay the advancement of the disease and ease symptoms [10]. The three general classes of drugs commonly used in the treatment of RA include non-steroidal anti-inflammatory agents, corticosteroids, and disease modifying anti-rheumatic drugs [11]. However, despite all the advancements in the pharmacological treatments, a complete and sustained remission of the condition is largely uncommon among this population [12].

Diet is a major modifiable determinant of chronic diseases and there is a large body of evidence showing that modifications to improve diet quality are directly associated with health benefits [13]. Diet is a topic of interest for people with RA and many have reported that certain foods can help alleviate symptoms and other foods may trigger ‘flare-ups’ leading to swelling, pain and stiffness [14]. There is data confirming positive effects of certain foods such as fish rich in n-3 polyunsaturated fatty acids (PUFAs) and the negative effects of certain unhealthy foods on symptoms of RA [15]. However, the existing evidence on diet and RA remains inconclusive and evidence based dietary guidelines for the management of RA are currently lacking. Recently, the French Society for Rheumatology established nine recommendations on diet for people living with RA which proposes the Mediterranean diet for people with chronic inflammatory rheumatic diseases and more specifically for people with RA mainly due to its beneficial effects on joint symptoms and cardiometabolic health [16].

The traditional Mediterranean diet (MedDiet) is characterised by a high content of vegetables, fruits, legumes, nuts, beans, cereals, grains, fish, and unsaturated fats such as extra virgin olive oil. The MedDiet is regarded as particularly healthy and is promoted for the management of several chronic disease states [17]. The effects of the MedDiet are well researched with many of its health related benefits attributed to its anti-inflammatory properties [18]. Although several case-control studies have suggested that higher consumption of fish, olive oil and cooked vegetables are associated with lower severity of RA [[19], [20], [21], [22], [23]], the evidence on the association between a MedDiet and symptoms of RA is limited. A systematic review including two clinical trials and two prospective studies demonstrated that a Mediterranean diet has beneficial effects in reducing pain and increasing physical function in people with RA [24]. More recently, a meta-analysis found that anti-inflammatory diets including a Mediterranean Diet resulted in notably lower pain compared to habitual diets in people with RA (−9.22 mm; 95% CI −14.15 to −4.29; p = 0.0002; 7 RCTs, 326 participants) [25]. Given these encouraging outcomes, additional studies are needed to explore whether a Mediterranean dietary pattern could improve physical function and quality of life in people with RA.

The telehealth approach for delivering dietary interventions is a safe, convenient and potentially a more inclusive way to capture diverse perspectives compared to face-to-face appointments with participants which is an essential consideration given the recent Covid-19 public health pandemic [26,27]. A systematic review including 23 studies demonstrated that telemedicine could offer a cost-effective and widely accepted approach to deliver consultations remotely in rheumatology [28]. Furthermore, according to Dietitians Australia position statement on telehealth, telephone-delivered dietary consultations are as effective as in-person consultations [29]. The MEDRA study aims to determine, through telehealth methods, the effect of implementing a MedDiet compared to a standard healthy diet as per the Healthy Eating Guidelines (HEG) in Ireland on physical function and quality of life of adults living with RA in Ireland. The specific objectives include (1) assessing the habitual dietary intakes and baseline diet quality of adults living with RA in Ireland; (2) investigating the effects of a MedDiet compared to a standard healthy diet on physical function and quality of life in adults with RA. Using semi-structured focus groups, at the end of the intervention period, the study will also (3) explore the participant experience of taking part in the MEDRA study and identify the self-perceived barriers and enablers towards adhering to the assigned diet.

## Methods

2

### Study design

2.1

The MEDRA study is a 12-week, parallel group, randomised controlled trial comparing two dietary interventions for the management of RA. This trial is designed in accordance with and adheres to the Consolidated Standards of Reporting Trials (CONSORT) statement [30]. Study participants will be randomly allocated to either a MedDiet group or the HEG group. Participants from both arms will attend five teleconsultations in total with the study Registered Dietitian (RD) over the 12-week intervention period on weeks 0, 3, 6, 9 and 12. For this study, blinding to intervention will not be possible but every effort will be made to manage participants in both groups as equally as possible. The primary endpoint is an improvement in physical function and quality of life of participants over the study period. The study design is detailed in Fig. 1.

**Fig. 1 fig1:**
[figure not shown]
Consort flow chart.

### Participant recruitment

2.2

Participants will be recruited through a collaboration with the patient organisation ‘Arthritis Ireland’ and through their social media platforms (i.e., Facebook, Twitter, Instagram) and from the outpatient rheumatology clinics at University Hospital Limerick (UHL) using poster advertisement.

### Participant eligibility

2.3

*Inclusion criteria*. Eligible participants will be aged ≥18 years with a definite diagnosis of rheumatoid arthritis according to American College of Rheumatology (ACR)/European League Against Rheumatism (EULAR) criteria [31]. Only English speakers who can complete questionnaires in English and with full access to smartphone or internet will be included in the study.

*Exclusion criteria*. Participants will be excluded if they:•Refuse or are unable to give informed consent to participate in the study;•Are women who are currently breastfeeding, pregnant or trying to become pregnant;•Have commenced nutritional supplements or a new dietary regime in the month prior to study enrolment;•Are participating in other studies which might affect their diet;•Have no access to smartphone or Internet

### Timeline of assessments

2.4

All participants will complete three video teleconsultations meetings through Zoom or Microsoft Teams at baseline, six and twelve weeks. Participants from both groups will also receive two telephone call follow up reviews at weeks three and nine. The video calls will be 30–45 min in duration while telephone call follow-ups will be between 10 and 20 min each. All calls will be delivered by the study RD. All participants will be informed of their diet allocation group during the baseline teleconsultation and will commence the diet the following day or as soon as is feasible for a period of 12 weeks. Participant information including demographic data, smoking status, medication and supplement consumption will be collected at baseline and checked at each video teleconsultation for changes. The baseline teleconsultation will consist of a nutrition and dietetic education session whereby the study RD explains the assigned dietary pattern to participants and how they will be following it over the 12 weeks study period. During the telephone call follow-up reviews, the RD will encourage participants to set three goals that focus on improving diet quality within their assigned diet or maintaining existing positive dietary habits. These goals will be reviewed and modified as needed at follow up sessions. The RD will also monitor participants’ compliance to the assigned diet using a 24-h recall which will be administered over the telephone at weeks three and nine. Table 1 outlines the schedule of measures at each time point.

**Table 1 tbl1:** Schedule of activities/measures for participants by week of study participation.

Variable	Instrument	Time point				
		Baseline (week 0)	Follow-up (week 3)	Mid-intervention (week 6)	Follow-up (week 9)	Post-intervention (week 12)
Diet intakes	3-day food diary	x		x		x
	24 -hour recall		x		x	
Diet adherence	MEDAS	x		x		x
	Healthy Eating Checklist	x		x		x
Quality of Life	RAQoL Questionnaire	x		x		x
Physical function	HAQ-DI	x		x		x
Anthropometric measures (weight)	patient-report	x		x		x
Anthropometric measures (height)		x				
Physical activity	YPAS	x		x		x
Medications and supplements	patient-report	x				
Smoking status	patient-report	x				
Ethnicity	patient-report	x				

Definition of abbreviations: MEDAS = Mediterranean Diet Adherence Screener; RAQoL = Rheumatoid Arthritis Quality of Life; HAQ DI = Health Assessment Questionnaire- Disability Index; YPAS= Yale Physical Activity Survey.

## Study procedures

3

### Screening assessment and randomisation

3.1

Prospective participants who express interest in the study will be contacted by the study RD who will administer a screening questionnaire over the phone. Once deemed eligible, the participant will receive a participant information sheet (PIS) and a consent form to sign and return. Next, participants will be randomly allocated into either a MedDiet group or HEG group using a permuted block randomisation scheme with 1:1 ratio allocation [32]. Randomisation is conducted by a statistician at the University of Limerick, who is not involved in the conduct of the RCT. Next, participants will be invited to complete the online questionnaires. A CONSORT flow chart of participants through the study is provided in Fig. 1.

### Dietary interventions

3.2

#### MedDiet group

3.2.1

The MedDiet intervention is based on components of the traditional Mediterranean diet which is primarily plant based and emphasizes intakes of fruits, vegetables and whole grains with the main added dietary fat being extra virgin olive oil (EVOO) [39]. The diet is rich in legumes and raw unsalted nuts, fermented dairy, fish and poultry with very little amounts of red meat [40]. Based on to the MedDiet guidelines and food pyramid, participants in this group will be advised to consume 60–80 ml of EVOO, at least two servings of vegetables and three servings of fruits daily. The study RD will advise participant to include fish at least 3 times a week and a handful of raw unsalted nuts every other day. Participants in the MedDiet group will be encouraged to include red wine in their diet. Red wine will be enjoyed with meals and in moderation (up to 7 glasses per week). Participants will be provided with a copy of a MedDiet guide specifically designed by the study RD to explain the components of the MedDiet. The guide includes the MedDiet food pyramid, 2-week meal plan, recipes, shopping list, ‘no-cooking’ meal options and general tips on how to follow and adhere to the diet. Meal plans and recipes were developed based on the MedDiet guide by Papamiltiadous et al., 2016 [41] with changes to reflect the Irish context.

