#### HEG group

3.2.2

Participants in this group will be advised to adhere to the current Irish Healthy Eating Guidelines [42] with particular emphasis on portion sizes, low fat options and healthy cooking methods. The current Healthy Food for Life – the Healthy Eating Guidelines and Food Pyramid have been developed by the Department of Health in Ireland. The food guide consists of a pyramid representing how different foods and drinks contribute towards a healthy balanced diet. Participants will be advised to limit foods that are high in fat, sugar, and salt to no more than once or twice a week. The diet also emphasizes the consumption of 5–7 portions of fruits and vegetables per day. All participants will be provided with resources to inform them of these guidelines and sample meal plans that are readily available on the Healthy Ireland website (HSE, http://www.hse.ie). A copy of the 101 Square Meals book from Safefood Ireland will be provided to participants in this group. The book includes shopping tips, food safety messages, menu planning advice as well as some healthy treats and snacks ideas. The book uses the Healthy Food for Life Guidelines to help individuals plan healthier meals and will help participants to have a varied and healthy diet while getting the best value for their money.

The diet will be modified and tailored to the participant's preferences by the study RD. This is first achieved based on the assigned diet and overarching principles, however within this, the RD works with the participants on a personal level to ensure the dietary recommendations were achieved. For example, if a person didn't like a recommended food, an alternative of equal nutritional value will be recommended based on participants' preferences. The RD will also manage participants who have allergies to specific food and food components. In the case of food allergies, the RD will evaluate and ensure the nutritional adequacy of an allergen-free diet and suggest appropriate substitutions or individual food replacements.

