## Outcome measures

4

The outcome measures and their corresponding timelines are presented in Table 1. Primary outcome measures include physical function and quality of life. Patient information including demographic data, smoking status, medication and supplement consumption are collected at baseline and any changes or additions in pharmacological treatment will be noted during the study period.

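### The MedDiet advice encourages red wine across the arm, and the article states no exception where a medical condition, medication or alcohol history makes alcohol unsuitable

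*Protocol article*

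**What the plan says.** The instruction is in section 3.2.1 (MedDiet group) of the protocol article: "Participants in the MedDiet group will be encouraged to include red wine in their diet". The next sentence sets manner and amount: "Red wine will be enjoyed with meals and in moderation (up to 7 glasses per week".

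The article describes three things that could keep a participant from receiving or following this advice:

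- Section 2.3 (Participant eligibility) excludes those who "Are women who are currently breastfeeding, pregnant or trying to become pregnant".
- Section 3.2.2 (HEG group) says: "The diet will be modified and tailored to the participant's preferences by the study RD". The paragraph is printed under the HEG heading but reads as if meant for both arms.
- The same section says: "The RD will also manage participants who have allergies to specific food and food components".

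The article also describes when relevant information is gathered. Under section 3.1 the study dietitian "will administer a screening questionnaire over the phone". Section 2.4 says that "medication and supplement consumption will be collected at baseline and checked at each video teleconsultation for changes", and section 4 that "any changes or additions in pharmacological treatment will be noted during the study period".

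**The concern.** The wine sentence is an active instruction to the arm as a whole. It is not conditional on the participant already drinking or on alcohol being medically suitable. The reference to moderation limits how much is taken, not who is advised to take it.

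The Background section describes people with RA as being on long-term drug treatment and often having other illnesses, including gastrointestinal disorders and depression. In such a group it is reasonable to ask whether alcohol suits the individual before encouraging it. Followed literally, the printed rule would encourage alcohol in a participant for whom it is unsuitable, unless the dietitian steps in on a basis the article does not state or the participant declines.

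What is at stake is participant safety. A secondary reason to correct the text is that others may copy the intervention from the published article.

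**Working it through.** No arithmetic settles this point: it depends on no power, effect-size or dropout figure. The check is to set each stated provision against the three grounds on which alcohol might be unsuitable.

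| Provision (section) | What triggers it | Medical condition? | Medication? | Alcohol history? |
|---|---|---|---|---|
| Exclusion criteria (2.3) | Pregnancy, breastfeeding, trying to conceive; also consent, recent supplements or new diet, other diet-related studies, no smartphone or internet | Only the pregnancy-related states | No | No |
| Tailoring of the diet (3.2.2) | Participant preference; a disliked food is the example given | Not stated | Not stated | Not stated |
| Allergy management (3.2.2) | Food allergy | Allergy only | No | No |
| Phone screen (3.1) | Content not shown | Unknown | Unknown | Unknown |
| Medication collection and checks (2.4, 4) | Drug use and changes are recorded | No | Recorded, but no consequence for the diet advice stated | No |

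Three things follow.

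1. Within the article, none of the provisions whose content is given withholds the wine advice on medical, medication or alcohol-history grounds, apart from the pregnancy-related exclusion.
2. The information needed for a medication-based exception is already gathered by the person who gives the advice. What is missing from the text is the link between the two.
3. The timing suits an exception. The phone screen comes before randomisation, so a question there would be asked of everyone in the same way. Medication is taken at baseline, when the diet is explained, and section 2.4 has it rechecked at the later video calls. The week-6 call is the one that matters for a change of drug, since week 12 ends the intervention. Table 1 marks medication at baseline only, so the text of section 2.4, not the table, supports the recheck.

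**The case against.** The strongest objection is that this is a condensed article. Cautions about a single food or drink would normally sit in the screening form, the information sheet or the dietitian's MedDiet guide, and none of these is shown. This stands in part: nobody can say from the article that no caution exists. It does not remove the point, because the article prints the instruction without a condition while describing other exceptions at the same level of detail. If an unseen caution exists, the printed rule should agree with it.

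Second, delivery is individual and professional. A registered dietitian makes every contact and knows the participant's medication; a rheumatologist collaborates; two ethics committees approved the study. Dislike of a food is given only as an example of tailoring, so the list need not be exhaustive. This also stands, and it makes literal application to a clearly unsuited person less likely. It still leaves the exception to unstated judgement.

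Third, the wording is already mild: wine is encouraged and not required, and seven glasses is a ceiling and not a target. That is correct and limits the severity.

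Fourth, the documents describe no specific hazard of alcohol with any RA drug or comorbidity. That is also correct. The point therefore rests on the general premise that alcohol is unsuitable for some people on medical grounds, and it names no particular interaction.

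**Conclusion.** The point holds as a minor matter of participant safety. The printed rule encourages wine across the MedDiet arm, and the article states no exception for a medical condition, medication or alcohol history. This rests on the article alone; the screening questionnaire or the MedDiet guide may already contain the exception.

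Three stronger readings are tempting and are not supported:

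- **That the trial has no safeguard.** The relevant materials are not shown, and the dietitian may use judgement.
- **That the number at risk can be estimated.** At 1:1 allocation the MedDiet arm is 44/2 = 22. Applying the Background's comorbidity range of 40 to 66% gives 22 × 0.40 = 8.8 and 22 × 0.66 = 14.5. A reader might infer that about 9 to 15 participants should not be offered wine. That range covers any comorbidity, comes from other studies and says nothing about alcohol. It measures neither unsuitability nor harm, and no count of affected participants can be derived from the documents.
- **That the results would be biased.** Nothing in the documents supports an effect of this rule on the HAQ-DI or RAQoL comparison, and none is claimed.

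**What to change.** Add to the wine sentence in section 3.2.1: *except where a medical condition, medication or alcohol history makes alcohol unsuitable, in which case the participant follows the MedDiet without wine.*

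Ask one question on this at the existing phone screen (section 3.1), and review the answer at the existing medication checks (sections 2.4 and 4). If the screening form or the MedDiet guide already covers it, only the article's wording needs to change.

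The change should stop there. Making wine optional for everyone, or dropping the encouragement for all non-drinkers, would alter the intervention for people with no medical reason and goes beyond the gap. The exception should not become an exclusion criterion: these participants remain eligible, randomised and analysed as allocated.

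The cost is one clause and one question on calls that already take place, with no added visits or staff and no change to sample size, randomisation or outcomes. The downside is that a few MedDiet participants would follow the diet without wine, so exposure to that one component is slightly less uniform.
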